# Confidentiality

At the point of consent to the trial, all participants will be allocated an identification code. Any data from which the identity of the participant could be determined will be kept securely on a password protected secure university network accessible only to members of the research team (henceforth described as the ‘university network’), or in a locked filing cabinet in the Human Nutrition Research Centre (quantitative data). Data collected through the qualitative process evaluation will be stored by a research associate in a locked cupboard in the Institute of Health and Society or on the university network.

Qualitative interviews will be audio recorded using a digital recorder. The digital files (raw data) will be sent to an external transcription company who have signed a confidentiality agreement with Newcastle University. Digital files will be sent in encrypted format using TrueCrypt © software. The transcription company will not have any information about the participants other than that included in the digital recording. The person transcribing the focus group will remove any information that could identify participants from the transcript, replacing such information with the participants ID code. Transcripts will be returned to the university in an encrypted digital format and will be stored on the university network. Quotes from qualitative interviews will be used to illustrate emergent themes from the data but these will be coded to hide the identity of the participant. Data will be treated in a way that is ‘non-attributable.

# Participant reimbursement

Participants will each receive a voucher (Eldon square) to the value of £50 for their participation in the trial. This figure matches current INVOLVE (ref) recommendations for reimbursement for participants in research who are not taking research-design or leadership roles. The current recommendations are for participants to receive a minimum £10 per hour. To ensure ethical and methodologically sound research, participants randomised to different arms of the trial should all receive equal financial reimbursement, even though some participants may be required to invest more time in research activities (e.g. if randomised to the intervention rather than control arm). Estimated research time varies from approximately 4 hours (two HAP assessments) in the control arm through to 6 hours (2 HAP assessments and interaction with the intervention) in the intervention arm of the trial. Therefore 5 hours (£50 reimbursement) represents an average amount of time spent on research activities across all participants.

# Insurance and finance

# dissemination

## Conferences

The quantitative and qualitative outcomes of this pilot trial will be presented at national and international conferences attended by multidisciplinary and varying audiences, including the EHPS, UKSBM, ISBNPA etc.

## Publications

The quantitative and qualitative outcomes of this pilot trial will be written-up for publication in peer-reviewed journals. Target journals included …

## Stakeholder event

The outcomes of this pilot trial will be disseminated at a final stakeholder event anticipated to occur in…

# Projected Timeline to conduct Pilot RCT

| **LEAP Pilot Timeline** | | | | | |  |  |  |  |  |  |  |  |  |  |  |  |  |  |  |  |  |  |  |  |  |  |  |  |
| --- | --- | --- | --- | --- | --- | --- | --- | --- | --- | --- | --- | --- | --- | --- | --- | --- | --- | --- | --- | --- | --- | --- | --- | --- | --- | --- | --- | --- | --- |
|  |  |  |  |  |  |  |  |  |  |  | **2013** |  |  | **2014** |  |  |  |  |  |  |  |  |  |  |  | **2015** |  |  |  |
|  |  |  |  |  |  |  |  | **Months** | | | Oct | Nov | Dec | Jan | Feb | Mar | Apr | May | Jun | Jul | Aug | Sep | Oct | Nov | Dec | Jan | Feb | Mar |  |
| **LEAP Pilot RCT** | | | | |  |  |  |  |  |  |  |  |  |  |  |  |  |  |  |  |  |  |  |  |  |  |  |  |  |
| Protocol development | | | | | | |  |  |  |  |  |  |  |  |  |  |  |  |  |  |  |  |  |  |  |  |  |  |  |
| University ethics approval | | | | | | | |  |  |  |  |  |  |  |  |  |  |  |  |  |  |  |  |  |  |  |  |  |  |
| Participant recruitment | | | | | | |  |  |  |  |  |  |  |  |  |  |  |  |  |  |  |  |  |  |  |  |  |  |  |
| Baseline assessment | | | | | |  |  |  |  |  |  |  |  |  |  |  |  |  |  |  |  |  |  |  |  |  |  |  |  |
| 2 month follow-up assessment | | | | | | | | |  |  |  |  |  |  |  |  |  |  |  |  |  |  |  |  |  |  |  |  |  |
| Qualitative interviews | | | | | | |  |  |  |  |  |  |  |  |  |  |  |  |  |  |  |  |  |  |  |  |  |  |  |
| Data analysis and 'data clinics' | | | | | | | | |  |  |  |  |  |  |  |  |  |  |  |  |  |  |  |  |  |  |  |  |  |
| Write-up pilot trial outcomes | | | | | | | | |  |  |  |  |  |  |  |  |  |  |  |  |  |  |  |  |  |  |  |  |  |
| Develop protocol for a definitive RCT | | | | | | | | | | |  |  |  |  |  |  |  |  |  |  |  |  |  |  |  |  |  |  |  |
| Develop funding application for RCT | | | | | | | | | |  |  |  |  |  |  |  |  |  |  |  |  |  |  |  |  |  |  |  |  |

**APPENDIX A**

**HAP battery**

*Equipment*

The following equipment will be required to conduct the assessment:

Laptop computer

Blood pressure monitor and stethoscope MicroLife watchBPhome

Portable spirometer (and consumables) Micro 1 Handheld Spirometer. Carefusion.

Weighing scale. Tanita TBF 300-MA

Portable stadiometer

Hydraulic hand Dynamometer. Baseline evaluation Instruments

9-hole pegboard. Rolyan

Measuring tape

Marking tape

Chronometer

CANTAB Touch Screen Tablet computer

*Assessment domains*

**Physical activity and inactivity**

An activity monitor, Axivity, will be used to assess physical activity and sedentary behaviour over seven consecutive days. The thin, waterproof device is attached to the participant on the back between L4 and L5. The device collects data on bouts of sedentary and ambulatory activity. After seven days, the participant will remove the device themself and send it back to the study team using a stamped address prepaid envelope.

**Dietary intake**

Dietary intake will be assessed using the multiple pass 24-hour recall method. In order to assess usual food intake, before and after interventions participants will be asked to complete a 24-hour dietary recall on three days, including two weekdays and one weekend day. In order to reduce possible effects of between-day variability in food intake, participants will be required to complete these dietary recalls on the same days of the week at each timepoint (eg Thursday, Friday, and Saturday; or Sunday, Monday, and Tuesday). An online diet questionnaire, the Oxford WebQ (Liu et al 2011), will be used. The Oxford webQ questionnaire takes around 15 to 20 minutes to complete. The Oxford WebQ is self-administered and assesses what participants ate and drank the previous day.

Five ageing-related domains will be will be evaluated in this study, physiological and metabolic health, physical capability, cognitive function, psychological wellbeing, and social wellbeing. The procedure for administration of the Health Ageing Phenotype (HAP) is explained in the HAP administration guidelines (appendix Z).

1. Physiological and Metabolic Health Domain

a) Blood pressure. Resting blood pressure will be measured in triplicate using a manual BP monitor. Before the measurement participants will be invited to rest in a sitting position for at least 10 minutes. An appropriate cuff size will be used for the measurement of each subject which will be used for all other measurements of BP.

b) Forced expiratory volume (FEV1). FEV1 will be assessed before and after interventions with a portable handheld spirometer (Micro 1). Briefly the participant will take in as deep breath as possible, when full place the mouthpiece in his/her mouth. Close his/her lips tightly around the mouthpiece. Blow through the mouthpiece into the spirometer, blowing air out as hard, fast, smoothly and completely as possible. Record the FEV1 from at least two and up to five technically satisfactory manoeuvres.

c) Waist and hip circumferences. Waist and hip circumferences will be measured using a measuring tape and following standardised protocols. Waist circumference will be measured midway between the uppermost border of the iliac crest and the lower border of the costal margin (rib cage). The tape should be placed around the abdomen at the level of this midway point and a reading taken when the tape is snug but does not compress the skin. In practice it may be difficult for very overweight patients to accurately palpate those bony landmarks in which case placing the tape at the level of the belly button is recommended. For hip circumference, identify the widest part of the buttocks. Then place the tape measure at this location and measure around the circumference of hips and buttocks.

d)Body weight and height. Body weight and height will be measured without shoes, after removing heavy garments and emptying pockets, using a portable scale and stadiometer. Waist to hip ratio and body mass index (BMI) weight/(height)^2^ will be estimated from these anthropometric measures.

2. Physical Capability Domain (Reuben 2013)

a) Handgrip strength. Hand-grip strength will be assessed in both arms at baseline and after intervention to measure the maximum isometric strength of the hand and forearm muscles. A lightweight and portable dynamometer will be used. The researcher will follow a specific protocol for the measurement of hand-grip strength (i.e. allowing one practice trial, and then record the best of three attempts with 30 seconds rest between each of these). The test takes approximately 3 minutes to administer

b) Gait speed. The 4-Meter Walk Gait Speed will be used as a measure of locomotion. Participants are asked to walk a short distance (4 meters) at their usual pace. Participants complete one practice and then two timed trials. Raw scores are recorded as the time in seconds required to walk 4 meters on each of the two trials, with the better trial used for scoring. The test takes approximately 3 minutes to administer (including instructions and practice).

c) Walk endurance test. The 2-Minute Walk Endurance Test is used as the measure of endurance. This test measures sub-maximal cardiovascular endurance by recording the distance that the participant is able to walk on a course in 2 minutes. The participant’s raw score is the distance in feet and inches walked in 2 minutes. The test overall takes approximately 4 minutes to administer (with instructions and practice).

d) Dexterity. A 9-Hole Pegboard Dexterity Test is used as a measure of dexterity. This simple test of manual dexterity records the time required for the participant to accurately place and remove 9 plastic pegs into a plastic pegboard. The protocol includes 1 practice and 1 timed trial with each hand. Raw scores are recorded as time in seconds that it takes the participant to complete the task with each hand (a separate score for each). The test takes approximately 4 minutes.

e) Standing balance test. The Standing Balance Test is a measure developed to assess static standing balance. It involves the participant assuming and maintaining up to 5 poses for 50 seconds each. The sequence of poses is: eyes open on a solid surface, eyes closed on solid surface, eyes open on foam surface, eyes closed on foam surface, eyes open in tandem stance. This test takes approximately 7 minutes to administer.

f) Sit-to-stand test. Participants start seated and then are timed standing up and sitting back down a 5 times and time will be recorded. Participants are usually encouraged to complete the test as fast as they can and are told to keep their arms folded. Participants will do one practice plus 2 timed trials.

g) Timed-up-and-go (TUG). Subjects asked to stand up from a standard chair with a seat height of between 40 and 50 cm, walk a 3-m distance at a normal pace, turn, walk back to the chair, and sit down. Timing measured in seconds began at the word ‘‘go’’ and ended when the subject’s back touched the backrest of the chair. Participants will perform three trials.

3. Cognitive Function

a) Executive function. Verbal and category fluency tests will be used to assess participants’ executive function. Within a set timeframe, usually one minute per letter participants are instructed by the experimenter to speak aloud as many words as possible that begin with a specific letter (phonemic fluency) – this is repeated 3 times for 3 different letters (e.g., CFL or PRW). In a separate one minute window, participants are then instructed to speak aloud as many words as possible which belong to a specific category, such as animals (category fluency). Participants will be audio-recorded when performing these tasks, to allow for detailed analyses of the responses made, including total number of words, repetition and errors. Completion of these tests takes approximately 5 to 7 minutes.

b) Episodic memory. The paired associates learning (PAL) CANTAB test will be used. Boxes are displayed on a touchpad screen. The participant watches as the boxes are ‘opened’ automatically, one by one, in a randomised order. One or more of them will contain a pattern. The patterns are then displayed in the middle of the screen, one at a time, and the participant must touch the box where the pattern was originally located. If the participant makes an error, the patterns are re-presented to remind the participant of their locations. The difficulty level increases through the test. The number of patterns increases from one (with 7 empty boxes) to eight (with no empty boxes), which challenges even very able participants.

Test administration takes approximately 10 minutes, depending on level attained. The PAL has 21 outcome variables including errors made by the participant, the number of trials required to locate the pattern(s) correctly, memory scores and stages completed. These data are produced automatically.

c) Processing speed. The letter-digit substitution test will be used to assess participants’ speed of processing. Participants complete this test using a pen and paper, upon which is presented a test grid and a key. The test grid is partially completed: a series of letters fills the top row of the grid, whilst the bottom row is blank. The key gives the numbers 1 to 9, each of which is paired with a different letter. Participants are required to fill in the blank boxes below the randomized letters with the appropriate digit indicated by the key, either by writing the digit in the response sheet or by speaking the digit aloud. The first 10 items are used as practice items, to ensure that participants understand the test instructions. After completion of these items, participants are instructed to replace the remaining items as quickly as possible. The key and the stimuli are the same for the oral and written versions of the test. Administration takes approximately 5 minutes. The number of correct substitutions made in 60 seconds is the dependent variable for both test versions. Responses can be given verbally or in writing (norms available for both), accommodating participants with motor limitations.

4. Psychological Wellbeing

a) Positive affect. The NIH Toolbox Positive Affect Survey will be used to assess participants’ levels of positive affect. This tool is administered via the NIH Assessment Center website. Items, displayed on a computer screen, ask about happiness, serenity, and cognitive engagement. The participant is asked to indicate agreement with each item using a 5 point Likert scale ranging from “not at all” to “very much”. Administration of this test takes 3-5 minutes; scoring and administration are automated. Computer adaptive testing is used in order to avoid practice effects

b) Life satisfaction. The satisfaction with life scale (SWLS) will be used. This tool is administered via the NIH Assessment Center website. Participants are prompted to rate 5 statements using a 7-point Likert scale to indicate the extent to which they agree with each statement (strongly agree to strongly disagree). The total is calculated automatically by the Assessment Center. Higher scores indicate greater satisfaction and administration of this test takes 1-2 minutes.

c) Quality of life. The control, autonomy, pleasure and self-realization, quality of life scale (CASP-19) will be used to assess participants’ multidimensional quality of life. This tool is administered via the NIH Assessment Center website. The test consists of 19 items relating to four theoretically-derived domains: Control (4 items), Autonomy (5 items), Pleasure (5 items), Self-realisation (5 items). Participants report the frequency with which they experience certain feelings or cognitions using a four-point Likert scale ranging from “Often” to “Never.” Items are scored automatically via the Assessment Center (with reverse coding of positive responses, so that higher scores equal higher QoL. The authors define the scale ranges as 0 (complete absence of QoL) to 57 (total satisfaction in all four domains). Administration of the test takes ~ 5 minutes

d) Mental health. The centre for epidemiological studies depression scale (CES-D) will be used to assess participants’ mental health, with a specific focus on depressive symptomatology. This test is administered via the NIH Assessment Centre. Participants are prompted to respond to 20 items by indicating the frequency with which they have experienced depressed mood, feelings of guilt, worthlessness and helplessness, psychomotor retardation, loss of appetite and sleep difficulties over the previous 7 days. Responses range from often (5 or more days out of 7) to not at all (one or zero days). Completion of the test takes approximately 5 minutes and the score is calculated automatically by the NIH Assessment Center.

5. Social Wellbeing (Gershon et al., 2010, Salsman et al., 2013)

We intend to use the following measurement tools, all of which will be administered via the National Institute of Health (NIH) Assessment Centre though a computer or smartphone and internet connection. The instruments can also be administered in paper and pencil format as short form instruments (typically from six to 14 items), although an inclusion criteria to the trial is that participants have access to the internet.

There is evidence that provision of explicit social roles (occupations) with group support can produce increased health and wellbeing in retirement (Heaven et al, 2013). However, a suitable instrument that assesses the perceived meaningfulness and satisfaction with explicit roles has not been identified. Consequently for use in the proposed pilot study we will use two versions (pre and post exposure) of a brief questionnaire developed by the research team. The questionnaire is currently untested and there is no psychometric information available regarding its properties. However, given the lack of appropriate measurement tools in this domain, it will collect self-reported expectation and (post intervention experience) of engaging in a social role/occupation. Currently the questionnaire is composed of 11 items in both (pre and post) versions and can be delivered online via the NIH Assessment Centre.

A link will be provided to the social relationships assessment tools at the NIH Assessment Centre. On following the link participants will be guided by text-based instruction through the assessment instruments. This will involve registering with the assessment centre (providing gender, and date of birth) and then entering an identification code and a password generated by the assessment centre. The participant will then follow onscreen instructions to complete the instruments which are presented sequentially will be included alongside measures of social wellbeing. Completion of both psychological and social wellbeing instruments takes approximately 8-10 minutes. The specific instruments are:

a) (PROMIS) companionship and social isolation scales: assesses perceived availability of someone with whom to share enjoyable social activities such as visiting, talking, celebrations, etc. It comprises 6 items, each with a scale 1-5 (Never to always). The PROMIS Social Isolation item bank assesses perceptions of being avoided, excluded, detached, disconnected from, or unknown by, others. This scale comprises 14 items, each with a scale 1-5 (Never to always).

b) PROMIS satisfaction with social roles scale: measures satisfaction with capacity to engage socially with family and friends and to perform social responsibilities. In total 44 items are available, however the respondent would only complete as many items as necessary in each bank to reach a level of internal consistency using Computerised Adaptive Testing (CAT).

c) PROMIS emotional and informational support bank: The PROMIS Emotional Support item bank assesses perceived feelings of being cared for and valued as a person and having confidant relationships. The PROMIS Informational Support item bank assesses perceived availability of helpful information or advice.

d) NIH toolbox meaning and purpose inventory: Meaning and Purpose is characterized by the extent to which people feel their life matters or makes sense. This tool comprises a total of 18 items rated on a 5-point Likert scale from strongly agree to strongly disagree.

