6. In the next five days, the trial administrator will telephone each eligible participant to answer any questions and to ascertain whether they would like to accept the invitation to participate. If there are any questions that can’t be answered over the phone by the administrator, a date for follow-up correspondence (either by e-mail or phone according to the preference of the potential participant) will be made. The administrator will request an answer to the question from the relevant trial team personnel, and will then relay this information to the participant during the arranged follow-up correspondence. On verbal consent, the trial administrator will ask that the participant sign the consent form and keep it until one of the research team visits them. The administrator will then schedule an appointment at a convenient time when one of the study team will visit the participant at their home or place of work to obtain the signed informed consent form and conduct the baseline assessment. The researcher will attend the appointment with spare consent forms in case the participant mislaid their original consent form.
7. Baseline assessment visit - after receiving informed consent, a member of the study team will administer the HAP battery assessment as per protocol (Appendix A). The activity monitor device will be attached to the participant, and it will be explained that the device is to be worn continuously for the next 7 days. The participant will be provided with a prepaid stamped address envelope to return the device after 7 days. The 24 hour recall dietary assessment tool procedure will be explained and participant will complete the first of three days to be recorded, and a web link to the social relationships tools will be provided. During this assessment session participants will be asked to provide information on smoking, alcohol consumption and demographic (Attachment 4 – Baseline data form).
8. The trial administrator will be informed by the member of the study team when baseline assessment is complete and the administrator will randomise the participant to one of the trial conditions recording key information (e.g. name, D.O.B. and assigned identification number) into a central database. A pedometer and instructions for its use will be posted to participants allocated to receive the LEAP intervention. The trial administrator will telephone or email the participant a few days later to check that the pedometer was received.

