9. Seven days after the trial administrator has confirmed that participants allocated to the LEAP intervention have received the pedometer, the trial administrator will email them a web link to access the intervention. They will also be provided with contact details of members of the study team to troubleshoot technical problems.
10. Immediately after the baseline assessment, the trial administrator will email a web link to the NHS LiveWell resource to participants allocated to receive the control intervention.
11. All participants will be reminded that they will be contacted again in approximately 6 weeks to arrange a follow-up visit by a member of the study team in two months’ time.
12. In the next three days, the trial administrator will telephone or email the participant to check that they received the web link to the intervention. During the call the administrator will arrange a date and time for a qualitative interview with those participants who have been identified as suitable using the purposive sampling procedure described in the qualitative protocol (see section 9). For participants randomised to the intervention group, the interview will be scheduled to take place no sooner than a week following the call to allow the participant to use the LEAP intervention and to ensure the interview is not conflated with use of LEAP. Approximately (n=6-8) appointments will be made with participants in the LEAP arm, and up to 4 appointments with participants in the control, with a further 6-8 and 4 appointments respectively being made toward the end of the trial. This will allow the research team to compare accounts of participation at the start and end of the trial respectively, potentially identifying unexpected participant expectations or disappointments/misunderstandings throughout the trial.
13. Six weeks after receiving the link to the LEAP or control intervention, the trial administrator will telephone participants to schedule an appointment at a convenient time in the next two weeks when one of the study team will visit the participant at their home or place of work to conduct the follow-up assessment. During the call the administrator will arrange a date and time for a qualitative interview with participants (n=6-8 in LEAP; n= 4 in control) who have been identified as suitable for a qualitative interview.

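### The diet-recall days are named by completion day, but the tool records the day before, so neither example pattern, followed as worded, captures two weekdays and one weekend day of intake

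*Protocol*

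**What the plan says.** Protocol, Appendix A, Dietary intake, makes three statements in one paragraph.

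- To capture habitual intake, participants are to "complete a 24-hour dietary recall on three days, including two weekdays and one weekend day".
- To limit between-day variability, "participants will be required to complete these dietary recalls on the same days of the week at each timepoint (eg Thursday, Friday, and Saturday". The examples in full are "eg Thursday, Friday, and Saturday; or Sunday, Monday, and Tuesday".
- The Oxford WebQ, the online questionnaire to be used, "assesses what participants ate and drank the previous day".

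STUDY Procedure, step 7, says that at the baseline visit the "participant will complete the first of three days to be recorded". Step 14 repeats the baseline procedure at follow-up. Step 13 has the administrator "schedule an appointment at a convenient time in the next two weeks" for that follow-up visit.

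The Length of follow-up text says that the behavioural data will feed the effect and sample size estimates for a later definitive trial, and that this pilot is not powered to detect change in them.

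**The concern.** The sentence with the examples governs when recalls are completed. The questionnaire describes a different day, the one before. Nothing in the paragraph says whether the named days are completion days or intake days, and nothing allows for the one-day lag. A field worker who follows the text literally will therefore collect intake for the wrong mix of days.

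The mix exists to represent habitual intake, so what counts is which days were eaten, not which days a form was filled in. If the lag is ignored, one group of participants has no weekend intake recorded and another has too much. That shifts estimated intake levels and adds spread between people that has nothing to do with diet. An unrecorded weekend day cannot be recovered in analysis.

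**Working it through.** **Inputs.** Required mix: "including two weekdays and one weekend day". Named patterns: Thursday/Friday/Saturday and Sunday/Monday/Tuesday. Lag: one day. All are from Appendix A, Dietary intake. Weekend means Saturday and Sunday. The documents give no value for D, the weekend-minus-weekday difference in intake.

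**Step 1. The plan's own figure.** Counting the named days as they stand, Thu/Fri/Sat has two weekdays and one weekend day, and so has Sun/Mon/Tue. The stated mix is reproduced if the lag is ignored, or if the names are taken as days eaten.

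**Step 2. Apply the lag (day eaten = completion day minus one).**

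| Completed | Eaten | Weekdays | Weekend days |
| --- | --- | --- | --- |
| Thu, Fri, Sat | Wed, Thu, Fri | 3 | 0 |
| Sun, Mon, Tue | Sat, Sun, Mon | 1 | 2 |
| Fri, Sat, Sun | Thu, Fri, Sat | 2 | 1 |
| Mon, Tue, Wed | Sun, Mon, Tue | 2 | 1 |

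The first two rows are the protocol's examples; the last two are the same examples moved one day later. Of the seven possible runs of three consecutive completion days, only those last two give the stated mix of days eaten.

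**Step 3. Is the mix reachable without that shift?** There are 10 × 2 = 20 sets of completion days with two weekdays and one weekend day (10 weekday pairs, 2 weekend days). A completion on Sunday or Monday records a weekend day; one on Tuesday to Saturday records a weekday.

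- Sets containing Saturday work only if Monday is also in the set: 4 sets.
- Sets containing Sunday work only if Monday is not: 6 sets.

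So 4 + 6 = 10 of the 20 also give the right mix of days eaten, all of them non-consecutive. Both of the protocol's examples are among the other 10.

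**Step 4. Error in level.** In a week the weekend has weight 2/7. The error in mean daily intake is (weekend share of the recalls − 2/7) × D.

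- Intended mix: 1/3 − 2/7 = 1/21, or +0.05D.
- First example: 0 − 2/7, or −0.29D.
- Second example: 2/3 − 2/7 = 8/21, or +0.38D.
- Two identical eaters, one on each pattern: 2/3 − 0, or 0.67D apart.

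**Step 5. Added spread.** Assume that D is the same for everyone and that a share p of participants use one example and 1 − p the other. The spurious SD is 0.67D × √(p(1 − p)): at p = 0.5 it is 0.33D, at p = 0.1 it is 0.67D × 0.3 = 0.20D, and if everyone uses one pattern it is zero.

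Let s be the between-person SD without this effect, and assume that pattern is unrelated to diet. At p = 0.5 the variance rises by the fraction (1/9) × (D/s)². Since D is not given, a range is assumed:

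- D/s = 0.25: 0.7%
- D/s = 0.5: 2.8%
- D/s = 1: 11.1%

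**Step 6. Change scores.** If a participant keeps the same weekdays at both timepoints, the error in Step 4 is the same at each and cancels from the difference.

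**The case against.** The strongest reply is that the paragraph is ambiguous, not wrong. If every named day is a day eaten, both examples give exactly the stated mix, and step 7 offers some support by speaking of days to be recorded. If every named day is a completion day, the mix is itself worded by completion and both examples again comply. This is fair, and it means the text does not contradict itself under either uniform reading. It does not remove the point. The first reading is not stated, and the sentence with the examples is about completing recalls. The second is consistent but defeats the purpose of the mix, which is habitual intake.

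A reader might also infer three stronger things, none of which the documents support.

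- *That booking follow-up at a convenient time contradicts the same-days rule.* The two-week window in step 13 contains every weekday twice, so both can be met. Step 13 does not remind the scheduler of the rule, and no more than that can be said.
- *That a visit on Tuesday, Wednesday or Thursday excludes any weekend day.* This needs consecutive recalls, and consecutive patterns appear only as examples. The questionnaire is online and self-administered, so the second and third recalls can fall on other days.
- *That the weekend mix will drift between timepoints and imitate or hide dietary change.* That would be a breach of the same-days rule, not something the protocol permits.

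It also stands that this is a feasibility pilot, not powered on diet, and that its questions about completion and missing data are largely untouched.

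**Conclusion.** The point holds as a wording fault with a real but limited consequence. Read as worded, the two examples capture none or two weekend days of intake instead of one. Intake levels are off by −0.29D or +0.38D against a true week, compared with +0.05D for the intended mix, and identical eaters on the two patterns differ by 0.67D. The added variance depends on D and on how participants divide between patterns, neither of which the documents give; over the assumed range of D/s from 0.25 to 1, with an even split, it is 0.7% to 11.1%. It matters because these data are meant to inform the definitive trial's sample size.

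Within-person change is unaffected where the same-days rule is kept, so the pilot's question about sensitivity to change is largely protected. The documents do not support treating this as a must-fix defect. Severity is minor to moderate.

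**What to change.** In Appendix A, Dietary intake, state that the two weekdays and one weekend day are the days eaten, and give the matching completion days: Friday, Saturday and Sunday for Thursday-to-Saturday intake, or Monday, Tuesday and Wednesday for Sunday-to-Tuesday intake. Allow non-consecutive completion where the visit weekday requires it. A rule that covers every case is that exactly one of the three recalls is completed on a Sunday or Monday and the other two on Tuesday to Saturday.

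As a minor addition, have step 13 book follow-up on a weekday compatible with the participant's baseline recall days.

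The cost is one paragraph, the participant prompt and the booking script, with slightly less flexible appointments. The change has to be made before data collection.
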